# Digitally Delivered Dietary Interventions for Patients with Eating Disorders Undergoing Family-Based Treatment: Protocol for a Randomized Feasibility Trial

**DOI:** 10.2196/41837

**Published:** 2023-01-26

**Keywords:** eating disorders, virtual treatment, dietary interventions, family-based treatment, anorexia, psychiatric disorder, digital health intervention, telehealth, virtual health

## Abstract

**Background:**

Eating disorders (EDs) affect 9% of the United States population, and anorexia nervosa (AN), specifically, has the second highest mortality rate of all psychiatric disorders. Yet, only 20% are able to access treatment. Access to care issues include long waitlists, lack of trained specialists, financial, and geographic barriers, all of which highlight the need for effective telehealth interventions. Family-based therapy (FBT) is a first-line treatment for adolescents and young adults with EDs, and weight gain early in treatment is considered a primary predictor of success with FBT. However, nutrition requirements for patients with EDs are uniquely complex. A variety of dietary interventions for guiding the renourishment process are used in practice, but empirical data on the effectiveness and acceptability of the various interventions are sparse. The significance of nutritional restoration and issues with access to first-line treatments underscore the need for further research exploring virtually delivered dietary interventions.

**Objective:**

Our objective is to compare the effectiveness and acceptability of 2 digitally delivered dietary interventions frequently used in eating disorder treatment settings: (1) calorie-based meal plans and (2) the Plate-by-Plate approach. Specifically, we will explore any potential differences in weight restoration achieved over 8 weeks of treatment as a primary measure of effectiveness, as well as additional treatment outcomes (ED symptoms, anxiety, depression, caregiver burden, and perceived effectiveness and acceptability for both caregivers and clinicians).

**Methods:**

Patients (N=100) with either AN or avoidant restrictive food intake disorders (ARFID) aged 6-24 years seeking treatment at a nationwide virtual eating disorder treatment program, were enrolled between May and August 2022. Upon admission, patients were randomly assigned to receive either the calorie-based intervention or Plate-by-Plate approach from their registered dietitian, all of whom have received training as study interventionists. While we were primarily interested in responses during the first 8 weeks of treatment, patients will be followed for up to 12 months. Descriptive statistics were used to describe patient characteristics and demographics. Weight changes and other treatment outcomes between groups will be compared using generalized linear models. Semistructured caregiver and clinician interview transcripts will undergo qualitative analysis.

**Results:**

Enrollment ran from March to August 2022, and we anticipate completion of data collection by November 2022. Analyses will be completed in January 2023.

**Conclusions:**

This study contributes to existing FBT literature by thoroughly exploring the acceptability of dietary interventions and their influence on weight restoration, an area in which research is sparse.

**International Registered Report Identifier (IRRID):**

DERR1-10.2196/41837

## Introduction

### Background

Eating disorders (EDs) are serious mental illnesses characterized by how one experiences a marked disturbance in weight and shape [1], afflicting people across all ages, genders, races, ethnicities, and body sizes. National prevalence estimates are 9%, and EDs have the second highest mortality rate (specifically anorexia nervosa [AN]) following opioid addiction [2]. The economic burden is also substantial, with an annual cost of US $64.7 billion [3]. Further, the COVID-19 pandemic has resulted in a staggering increase in new ED cases, as well as exacerbation of ED symptoms and decreased motivation for recovery for those with preexisting EDs [4,5]. The rise in demand and challenges with access to care were compounded by long waitlists, lack of trained specialists, financial and geographic barriers, and underscored need for improving access to effective ED treatments [6].

Telemedicine or digitally delivered ED treatment options offer an opportunity to meet the rising demand while addressing geographic barriers and providing patients with timely access to trained specialists and reduce barriers associated with accessing care. Telemedicine ED treatments have been on the rise primarily as a result of the COVID-19 pandemic, and recent research supports their effectiveness and comparability to in-person care [7-11]. Family-based treatment (FBT) is an approach through which caregivers are tasked with renourishing their child at home while given guidance by a team of specialists. FBT is a first-line treatment for adolescents and young adults with AN and shows promise as an effective modality for other ED subtypes as well [12,13]. Recent research supports the efficacy of digitally delivered FBT as outcomes rival those of in-person treatment options [14-16]. Nutritional restoration is a central treatment element across all ED subtypes, and weight gain in the first several weeks of FBT is considered a primary predictor of remission [17,18]. However, nutrition requirements for patients with EDs are uniquely complex and varied, with kilocalorie needs reaching 70-100 kcal per kg per day, and caregivers generally require ongoing support to successfully navigate home-based refeeding. The importance of nutritional restoration for remission highlights the need for a better understanding of the dietary interventions most commonly used in ED treatment settings. While the inclusion of the registered dietitian (RD) on multidisciplinary teams is standard in other ED treatment settings and modalities aside from FBT, historically, FBT was led by a family therapist who was also responsible for giving guidance around feeding. In recent years, the need for specialized nutrition support has become more apparent, and the presence of RD is more commonplace. The RD can skillfully address issues that arise in treatment (management of malnutrition, refeeding syndrome, weight plateaus, erroneous belief systems around food and weight, lack of diversity in food choices, and needs adjustments for patients return to sport) that may be unaddressed by therapists, but are vital for achieving remission [19,20]. Additionally, the RD assists by giving guidance on optimization of energy density, determination of goal weight range, alleviation or management of physical symptoms that arise secondary to refeeding, and identification of nutrients of concern, which is of particular importance for patients with avoidant restrictive food intake disorder (ARFID) [21]. However, a variety of dietary interventions are used in practice across the ED field, and the evidence comparing effectiveness of dietary approaches, in person or digitally delivered, is sparse.

### Dietary Interventions

An overview of the interventions most commonly used in practice when treating ED patients are as follows:
1. Daily Calorie Target: caregivers or patients are provided a daily kilocalorie goal, and generally, the number of meals and snacks will also be prescribed, each with an associated kilocalorie goal. Provision of a daily calorie goal and discussions of calories in foods are generally discouraged in settings, where dietary interventions are patient-facing, as doing so may exacerbate ED thoughts and behaviors. Calorie targets may, however, be provided to caregivers as a means of guiding home-based refeeding efforts.

2. Plate-by-Plate approach: the Plate-by-Plate is a visual approach with primary intent for use in FBT, whereby caregivers are instructed to serve “normal” portions or plates versus using calories to guide meal or snack planning (Multimedia Appendix 1). This approach is regarded as a more flexible and intuitive, as calorie counting and measuring are discouraged. For patients requiring weight restoration, caregivers are instructed to create a plate consisting of 50% starch, 25% protein, and 25% vegetables and fruits, with dairy and fat servings specified by the RD for the meals. Key features of this approach include primary caregivers making the decision around what and how much to serve, with an emphasis on dietary variety and exposure to all foods. These features are thought to be important as they uphold parental empowerment, a core tenet of FBT [22].

3. Exchange system: this approach is most widely used in residential and partial hospitalization programs, where guidance is given directly to the patient [22]. The exchange system was developed by the American Diabetes Association as a way to categorize foods into 6 groups, and each “exchange” in a given food group is associated with a particular macronutrient range [23]. For example, 1 dairy exchange can be 1 oz of cheese or 8 oz milk. A number or range of exchanges are assigned to each meal and snack, thereby encouraging the patient to consider balance and dietary variety. The exchange system is seldom used in FBT given the different needs of caregivers versus patients.

This feasibility study will compare the acceptability of 2 digitally delivered dietary interventions and preliminary effectiveness in early stages of treatment: (1) calorie-based meal plans and (2) the Plate-by-Plate approach [24]. Our primary outcome of interest is weight restoration achieved after 8 weeks of treatment, as this is the best predictor of remission. We will also examine the following treatment outcomes by intervention: ED symptoms, anxiety, depression, caregiver burden and self-efficacy, and caregiver’s acceptability and perception of effectiveness. Acceptability and perceived effectiveness will also be measured for clinicians once week 8 outcomes have been captured for all participants. While we are most interested in early treatment response, patients will be followed and clinical outcomes for patients and caregivers reported throughout the entirety of their treatment course as part of standard practice. We anticipate that the findings from this study will help us better understand the needs and experiences of caregivers undergoing FBT and ultimately, whether 1 approach is superior in terms of influence on treatment outcomes. We will also gain insight around commonly held assumptions, such as the running hypothesis that providing caregivers with a calorie target may undermine parental empowerment and self-efficacy. This study will add to existing FBT literature by exploring the impact of dietary interventions that guide caregivers' process for renourishing their child, for which there is currently no research.

## Methods

### Participants

We will examine the aspects of treatment outcome in patients aged 6-24 years self-selecting for web-based ED treatment at Equip Health. The inclusion criteria are as follows: (1) aged 6-24 years, (2) ED diagnosis of AN or ARFID, (3) consented to participate in treatment approach comparison research upon admission, (4) apparent need for weight restoration upon admission, (5) first time recipients of treatment at Equip Health, and (6) assigned to RD interventionist.

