#### Weight

Upon admission, caregivers receive instructions from their assigned Equip medical provider on proper procedure for checking weight. Weights are taken in the morning, after voiding, prior to any oral intake and patients are asked to wear light clothing. The patient’s weight (in pounds) is taken twice weekly by caregivers and communicated via text message from caregivers to Equip’s Health Insurance Portability and Accountability Act–compliant medical record platform. For each patient, the RD calculates a target weight for weight restoration. Target weight is calculated using expected weight data from each patient’s CDC BMI-for-age Growth Charts. Our primary end point of interest is weight change during the first 8 weeks of treatment, which will include an average weekly rate of weight gain and total weight change from admission to treatment week 8.

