### Statistical Analysis

The treatment outcomes will be collected via our Health Insurance Portability and Accountability Act–compliant medical record platform and will be extracted by trained research personnel. Descriptive statistics will be used to describe patient characteristics and demographics of our patients and treatment outcomes defined in Table 1. To examine any differences in effectiveness between the 2 interventions, we will compare the rate of weight change between the groups using generalized linear models in R version 4.1.1 (R Core Team). We will also look at outcomes across ED subtypes.

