### Procedures

Upon beginning treatment at Equip Health, eligible patients will be randomly assigned to receive either the calorie-based approach or the Plate-by-Plate intervention within their first 1-2 sessions with their assigned RD. In the first phase of treatment, the RD meets exclusively with caregivers (eg, parents or guardians) at a weekly meeting cadence for the first month, and thereafter in accordance with the RD’s judgment.

A high-level summary of each approach is as follows: (1) calorie-based nutrition prescription: following the completion of a nutrition assessment by the RD, caregivers will be prescribed a calorie goal and be instructed to aim to reach that goal daily as a primary focus of treatment. In collaboration with caregivers, a calorie goal will be assigned to 3 meals and 3 snacks daily. For example, the goal may be 3000 kcal per day, comprised of 700 kcal meals 3 times per day, and 300-kcal snacks 3 times per day. Additionally, caregivers are provided 7-day sample menus that align with their calorie prescription. If clinically indicated, they may also receive education on how to increase the caloric density of meals while maintaining low volume. Adjustments will be made throughout the treatment course to calorie prescriptions per RD’s judgment to accommodate the weight restoration goal of 2 lbs per week. During the initial session, caregivers are instructed to send photos and density estimates of all foods consumed by the child to the RD, and feedback will be given speaking to the adequacy of calorie content of meals and snacks in the follow-up sessions. (2) Plate-by-Plate approach is summarized for caregivers in the following steps:

Choose 10-inch platePlate all food groupsFill plateParent decides number of meals or snacksInclude varietyDoes the meal make sense?Final review: Does the plate make sense?

Caregivers are instructed to prompt the patient to complete the plate, and in the case of food refusal, oral supplements are provided to replace the remaining food.

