## Results

### Demographics

A total of 100 patients (with average age of 15 years) were enrolled on a rolling basis from March through August 2022. Fifty patients were assigned to the Plate-by-Plate group and 50 to the calorie target group. Overall, 83% of participants were cisgender females, 9% were cisgender males, 6% were nonbinary, and 2% were transgender. Furthermore, 66% of participants were diagnosed with AN restricting subtype, 18% with the AN binge-purge subtype, and 16% with ARFID. We anticipate completion of data collection by November 2022 and analysis by January 2023.

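### Entry needs no minimum weight deficit, so patients less than 16 lb below target can reach it within the 8-week window and dilute the arm comparison; adjust the primary model for admission deficit

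*Protocol article*

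**What the plan says.** Under Participants, the fourth inclusion criterion is an "apparent need for weight restoration upon admission". The article gives no threshold and no reference measure for it.

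Under Weight: "For each patient, the RD calculates a target weight for weight restoration", using growth-chart data. The same section fixes the endpoint: "Our primary end point of interest is weight change during the first 8 weeks of treatment", to include "an average weekly rate of weight gain and total weight change from admission to treatment week 8". Weights are recorded in pounds, twice weekly. The target weight enters neither the criterion nor the endpoint.

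Under Procedures, the calorie-based arm has its prescriptions adjusted "to accommodate the weight restoration goal of 2 lbs per week". The Plate-by-Plate description gives no pace.

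Under Statistical Analysis: "we will compare the rate of weight change between the groups using generalized linear models". No baseline covariate is named. Under Demographics: "Fifty patients were assigned to the Plate-by-Plate group and 50 to the calorie target group". Enrolment is therefore complete.

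**The concern.** A change score over a fixed window compares two approaches best when every patient has room to respond for the whole window. The criterion as stated does not ensure this. A patient a few pounds below target can finish restoration early. If gain then slows or stops, that patient's week-8 change is limited by the deficit however quickly it was made up.

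Where one approach truly works faster, more of its patients meet the limit, and the observed difference is smaller than the true one. The article hopes to learn whether one approach is superior and to name a preferred one. The risk is therefore a missed or understated difference, with only 50 patients per arm. Ages run from 6 to 24 years, so deficits in pounds probably vary widely.

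**Working it through.** **1. The plan's own figures.** The article gives no power, effect size or standard deviation, so there is no design figure to reproduce. The inputs it does give are 2 lb per week (Procedures, calorie arm), 8 weeks (Weight) and 50 per arm (Demographics).

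**2. Break-point.** 2 lb/week × 8 weeks = 16 lb. A patient with deficit D who gains 2 lb per week reaches target at week D/2. If gain stops there, the average rate over 8 weeks is D/8.

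| Deficit (lb) | Week target is reached | Average rate over 8 weeks (lb/week) |
|---|---|---|
| 6 | 3 | 0.75 |
| 10 | 5 | 1.25 |
| 12 | 6 | 1.50 |
| 16 | 8 | 2.00 |

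At 1 lb per week the break-point falls to 8 lb.

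**3. Size of the dilution (assumed inputs).** Take 8-week gain = min(8 × rate, D). Mean rates are 1.5 and 1.0 lb per week with between-patient SD 0.6, and the deficit is lognormal with log-SD 0.6. Without the cap the difference is 8 × 0.5 = 4.0 lb, the SD is 8 × 0.6 = 4.8 lb, and the standardised difference is 4.0/4.8 = 0.83. With 50 per arm and two-sided 5% (assumed), power = Φ(0.83 × √(50/2) − 1.96) ≈ 0.99. With the cap, by simulation:

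| Median deficit (lb) | Reach target, faster / slower arm | Difference (lb) | SD (lb) | Standardised difference | Power |
|---|---|---|---|---|---|
| 10 | 57% / 36% | 2.15 | 3.9 | 0.55 | 0.78 |
| 15 | 35% / 19% | 2.9 | 4.3 | 0.68 | 0.93 |
| 25 | 13% / 6% | 3.6 | 4.6 | 0.79 | 0.98 |

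The SD falls as well, so the loss on the standardised scale (34%, 18%, 5%) is smaller than the loss in pounds (about 46%, 27%, 10%).

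**4. Other assumptions.** The rate pairs were 2.0 v 1.5 (SD 0.9), 1.5 v 1.0 (SD 0.9) and 1.2 v 0.8 (SD 0.7), with log-SD of deficit 0.5. Uncapped power is 0.79 to 0.81. At a median deficit of 8 lb, 27–54% of the difference is kept; at 16 lb, 61–84%; at 30 lb, 89–97%. Power runs from 0.26 to 0.81 over this range.

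**5. No true difference.** If both arms share the same distribution of rates, random allocation gives min(8 × rate, D) the same distribution in each. The expected difference is then zero.

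**6. What adjustment buys.** In the model of step 3 with a 10 lb median, adding admission deficit leaves the difference at 2.15 lb. The residual SD falls from 3.9 to 3.5 lb with deficit entered linearly, or to 3.3 lb on the log scale. The standardised difference rises from 0.55 to 0.61 or 0.65, and power from 0.78 to 0.86 or 0.90. At a 25 lb median the gain is negligible (0.79 to 0.79 or 0.80). Adjustment recovers precision; it does not undo the dilution.

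**The case against.** The case against is substantial.

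- **Nothing shows that patients do reach target by week 8.** No admission deficits are reported. Strengths and Limitations says individual nutrition work generally begins only after renourishment has gone on for several months, which suggests that many patients are still below target at week 8. That points to the milder rows above. This stands, and it leaves the size open.
- **Stopping at target is an assumption.** The article does not say what happens to weight after target, and the pace appears in one arm only. This stands.
- **The endpoint answers the stated question.** The objective is restoration achieved over 8 weeks. If both approaches restore mildly underweight patients in that time, similar totals are a true answer. This stands, and is why the endpoint should be kept.
- **The full protocol may define the criterion.** It may, and the lack of a definition in a condensed article is not the point here. The point is that the criterion and the endpoint, as both are stated, leave room for a ceiling.

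A reader might go further and infer three things that the documents do not support:

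- *That 8-week gain measures the deficit rather than the approach.* At most this applies to the total change of patients who reach target. Their earlier twice-weekly weights still reflect the approach, and the article does not say that the rate is simply total change divided by 8.
- *That the cap adds spread.* In the model it reduces the SD, from 4.8 to 3.9 lb at a 10 lb median.
- *That the comparison is biased towards one arm.* Allocation is random, so step 5 applies.

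**Conclusion.** The point holds as a possible ceiling. Entry sets no minimum shortfall from a target weight that is calculated for every patient, and at the stated pace any deficit under 16 lb can be made up within the primary window. The consequence is dilution towards zero and some loss of power.

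The size cannot be fixed from the article. On the assumptions shown, it runs from almost nothing (median deficit 25 to 30 lb) to a loss of about half the difference or more (8 to 10 lb). All of these figures assume that gain stops at target, and any continued gain would make the loss smaller. This does not undermine the trial's validity. It is a reason for an inexpensive improvement to the analysis and for reporting that lets readers judge whether a ceiling occurred.

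A reader might also infer that the eligibility criterion must be rewritten. With all 100 patients already enrolled, that would change nothing for this trial.

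**What to change.** Keep the 8-week endpoint and all 100 randomised patients.

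1. Add admission deficit (target weight minus admission weight) as a prespecified baseline covariate in the primary model. Fix its functional form in advance; a log scale fails for any patient at or above target on admission. Staff who do not know the arm should derive or confirm the target from the growth-chart data, because the treating dietitian sets it.
2. Report admission deficit by arm, and the number in each arm at or above target by week 8.
3. As sensitivity analyses only, show (a) the comparison in patients with a deficit of at least 16 lb and (b) the rate of gain up to target. Analysis (a) uses a baseline value, so the comparison stays randomised, but it has fewer patients. Analysis (b) answers a different question and tends to pick out upward measurement error: with assumed noise of 1 to 1.5 lb and a 10 lb median, true rates of 1.0 and 1.5 come out between 1.07 and 1.57 and 1.18 and 1.74, so the arm difference is roughly kept (0.50 to 0.56).

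The cost is analysis wording plus extraction of target weights and twice-weekly weights that the article says are already produced. The article dates completion of the analysis to January 2023, its own month of publication. If outcomes by arm have already been examined, the adjusted model should be reported as added afterwards.
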